### Data collection

At baseline, medical history (including clinical signs and symptoms, duration of the neurological deficit, number of attacks, previous cardiovascular events, previous cardiovascular treatments, vascular risk factors, and medication) will be assessed and clinical and neurological examination (including blood pressure) will be carried out. The baseline neurological and functional status will be assessed with the National Institutes of Health Stroke Scale (NIHSS) and with the modified Rankin Scale [10,13]. The vascular risk factors (hypertension, smoking, diabetes, lipid disorders) will be noted. Laboratory investigations will include complete blood count, erythrocyte sedimentation rate, C-reactive protein, and cholesterol.

The degree of stenosis in the vertebral artery will be assessed with duplex ultrasound and MRA, CTA, or conventional angiography. Except for duplex ultrasound, the degree of the stenosis will be calculated by dividing the residual lumen (N) by vessel diameter at a point distal to the stenosis where the normal vessel calibre has been restored (D), and applying the formula: (1 - N/D) × 100% = degree of stenosis [14]. To assess the location of stenosis, the vertebral artery is divided into four sections: V1-V3 form the extracranial vertebral artery and V4 forms the intracranial vertebral artery [15]. The type of plaque in the vertebral artery and the presence and degree of stenosis in other brain feeding arteries will be noted.

CT and MRI scans will be performed to investigate the presence and type of a cerebral infarct (supply territory of intracerebral artery, small vessel disease, large vessel disease)

### Follow-up

Follow-up visits will be performed at one day and at 1, 6, and 12 months after stenting (or randomisation in the conservative treatment group) and every year thereafter. The close-out visit of each patient will be scheduled one year after randomisation of the last patient.

Follow-up data to be obtained at one day and after 1, 6 and 12 months, every year thereafter, and at close out will include:

1. the occurrence and type of vascular event;

2. complications associated with the endovascular procedure;

3. medication;

4. blood pressure;

5. score on the modified Rankin Scale;

6. the degree of (re)stenosis assessed with duplex ultrasound and CTA will be assessed after one year and following an ischaemic stroke.

### Statistical considerations

With 90 patients in the endovascular intervention arm, a complication rate of 7.8% (7 events) would yield a 95% confidence interval from 3.2 to 15.4%. The estimate of 7.8% is comparable to that of 8.2% for carotid stenting [8]. As the number of patients receiving angioplasty without stent placement is expected to be extremely small, these patients will be analysed together with the patients who have received a stent.

Inclusion of a total of 90 patients in the medical arm during three years and one final year of follow up for these patients will provide 225 patient years of follow up. This number of patient years would yield a 95% confidence interval of 4.1 to 11.5% for an annual event rate of 7%.

An additional analysis will be done to compare the incidence of vascular events between the two treatment groups. This analysis will be based on the intention-to-treat principle and reported in terms of the hazard ratio with corresponding 95% confidence intervals calculated with the Cox proportional hazard model.

We consider the precision of the above estimates sufficient for reliable calculation of the sample size of a conclusive randomised clinical trial.

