In patients with carotid stenosis of 50% or greater, carotid endarterectomy (CEA) leads to an absolute reduction in the 5-year cumulative risk of ipsilateral carotid ischaemic stroke and any stroke or death within 30 days after surgery of 8.5% (95% CI, 5.6 – 11.3) [5]. Two large randomised clinical trials are currently studying carotid stenting as an alternative to CEA. Based on large case series, it is hypothesized that the trials will demonstrate the equivalence of carotid stenting as compared with CEA. By contrast, the benefit of revascularisation of vertebral stenosis is fully uncertain. Surgery to this artery is difficult due to poor access and is not considered in most centres [6]. In the last decade, treatment of vertebral stenosis by percutaneous transluminal angioplasty, usually with stent placement, has been introduced as an attractive alternative to surgery.

The endovascular access to the vertebral artery is relatively easy and the procedure can be performed without general anaesthesia, enabling continuous neurological monitoring of the patient. However, the procedure also has disadvantages. The major risk of endovascular treatment is dislodgement and distal embolisation of plaque and thrombotic debris, which may lead to stroke. In a recent review of reports on 331 endovascular treatments of vertebrobasilar stenosis, the 30-day risk of TIA, stroke, or death was 6.4% [6]. In another review of stenting procedures for vertebral or basilar artery stenosis reported up to 2005, the periprocedural risk of stroke or death was 1.6% for proximal vertebral artery stenosis and 13.8% for distal VB stenosis [7]. After a mean follow-up of one year, restenosis had occurred in one quarter of the cases of proximal vertebral artery stenting. The difference in complication rates in the treatment of proximal versus distal vertebral artery stenosis is most likely the result of several factors. First, studies of distal VB artery stenosis included lesions of the basilar artery as well. In addition, the distal procedures were much more frequently performed in the acute phase of VB artery thrombosis, and antithrombotic treatment strategies were different. For this reason, there are no reliable data on stenting of the distal vertebral artery after the acute phase.

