### Randomisation

A total of 180 patients will be included in the study. Patients will be randomised to either the combination of vertebral artery stenting and best medical treatment or best medical treatment alone with use of a web-based randomisation system, which includes a minimisation algorithm [12]. Randomisation will be stratified by centre and location of the stenosis (origin vs. more distal parts of the vertebral artery).

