### Safety and indemnity

The major risk of endovascular treatment is dislodgement and distal embolisation of plaque and thrombotic debris, which may lead to stroke. In a recent review of reports on 331 endovascular treatments of VB artery stenosis, the 30-day risk of TIA, stroke, or death was 6.4% [6]. In another review of stenting procedures for vertebral or basilar artery stenosis reported up to 2005, the periprocedural risk of stroke or death was 1.6% for proximal vertebral artery stenosis and 13.8% for distal artery stenosis [7]. Other neurological complications, such as vertebral artery dissection, occurred in 2.6% and 6.0% of the cases, respectively, and non-neurological complications, such as inguinal haematoma, in 1.3% and 2.8%. As mentioned above, the complication rates for distal VB stenting do probably not apply to stenting of the distal vertebral artery outside the acute phase of posterior circulation ischaemia. After a mean follow-up of one year, restenosis has been reported to occur in one quarter of the cases of proximal vertebral artery stenting. However, case series are prone to publication bias and the percentages reported may be different in daily clinical practice. In all randomised trials on carotid stenting versus CEA, the 30-day incidence of any stroke or death was 8.2% (126/1492) after stenting [8]. Moreover, a limitation in interpreting data on vertebral artery stenting is the absence of data describing the risk of recurrent stroke in patients with vertebral stenosis on best medical therapy alone.

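### Stenosis location is an allocation factor, but the article describes only a pooled 30-day complication rate and a Cox model with no stratum; report the rate by location and stratify the model

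*Protocol article*

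**What the plan says.** - **Allocation** (Randomisation): patients are allocated by a "web-based randomisation system, which includes a minimisation algorithm", and "Randomisation will be stratified by centre and location of the stenosis (origin vs. more distal parts of the vertebral artery".
- **Safety estimate** (Statistical considerations): "With 90 patients in the endovascular intervention arm, a complication rate of 7.8% (7 events) would yield a 95% confidence interval" of 3.2 to 15.4%. This is one rate for the whole arm. The section then judges the precision of its estimates good enough for sizing the later trial.
- **Between-arm comparison** (Statistical considerations): "An additional analysis will be done to compare the incidence of vascular events between the two treatment groups". It is by intention to treat and gives a Cox hazard ratio with 95% interval. No covariate or stratum is named, and none is ruled out.
- **Safety criterion** (Adverse event reporting): one complication rate, whose lower confidence limit is set against a single figure of 8.2%.
- **Risk by location** (Background): "1.6% for proximal vertebral artery stenosis and 13.8% for distal VB stenosis". The Discussion gives, from the same review, neurological complications of 5.5% (extracranial) and 17.3% (distal, intracranial).
- **The plan's own caveats:** Background says "there are no reliable data on stenting of the distal vertebral artery after the acute phase". Safety and indemnity says "the complication rates for distal VB stenting do probably not apply to stenting of the distal vertebral artery outside the acute phase".

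**The concern.** The investigators thought location important enough to balance on, and their cited figures all point to higher risk for distal lesions. Yet no section describes a complication rate by location. The Ethical considerations call finding the rates of adverse outcomes the major aim of the trial, and the results are meant to size a definitive one. Two things are at stake.

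- **Transfer.** If risk differs by location, the pooled rate is a weighted average with weights set by who happened to be enrolled. The interval of 3.2 to 15.4% covers sampling error in that average. It does not cover a change of mix in the next trial.
- **Safety signal.** An excess confined to a small distal group is diluted in the pooled rate, the only form in which the safety criterion is written.

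A lesser matter is the Cox model. When a strongly prognostic factor has been balanced at allocation, leaving it out of the model pulls the hazard ratio towards 1 and makes the test conservative.

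**Working it through.** **1. The plan's figures.** The exact (Clopper-Pearson) interval for 7/90 = 7.8% is 3.2 to 15.4%, as stated. Follow-up is 90 × (1.5 + 1) = 225 patient-years, as stated. The exact Poisson interval for 16 events in 225 patient-years (0.07 × 225 = 15.75, rounded up) is 4.1 to 11.5%, as stated. No figure in the section is wrong.

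**2. Contrast by location in the cited review.** Stroke or death: 13.8/1.6 = 8.6. Neurological complications: 17.3/5.5 = 3.1.

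**3. Pooled rate by mix.** Let f be the distal share. The article does not give it, so a range is shown. Pooled rate = (1 − f) × proximal rate + f × distal rate.

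| f | from 1.6% and 13.8% | from 5.5% and 17.3% |
|---|---|---|
| 10% | 2.8% | 6.7% |
| 20% | 4.0% | 7.9% |
| 50% | 7.7% | 11.4% |
| 67% | 9.8% | 13.4% |

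For example, at f = 20%: 0.8 × 1.6 + 0.2 × 13.8 = 1.28 + 2.76 = 4.04%. The second pair is a different endpoint. It is there to show that the dependence on mix does not rest on the 8.6-fold ratio alone.

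**4. How pooling can hide an excess.** Assume 20% distal, so 72 origin and 18 distal patients, and invented counts of 1 and 5 events. Exact 95% limits:

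- Origin: 1/72 = 1.4% (0.04 to 7.5%).
- Distal: 5/18 = 27.8%, lower limit 9.7%.
- Pooled: 6/90 = 6.7%, lower limit 2.5%.

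The pooled lower limit is well below 8.2%, while the distal one is above it.

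**5. Cox model with and without a location stratum.** Simulated trials, 90 per arm, balanced on location, one to four years of follow-up. The location effect on hazard is an assumption, since the article gives none for medical or long-term risk.

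| Assumed location effect | Distal | True HR | Rejected, unadjusted | Rejected, stratified |
|---|---|---|---|---|
| 8.6-fold, both arms, throughout | 50% | 1 | 3.3% | 4.6% |
| 8.6-fold, both arms, throughout | 50% | 2 | 46% | 54% |
| 8.6-fold, both arms, throughout | 20% | 1 | 2.5% | 4.6% |
| 8.6-fold, both arms, throughout | 20% | 0.5 | 20% | 27% |
| 8.6-fold, both arms, throughout | 50% | 0.5 | 29% | 31% |
| 2-fold, both arms, throughout | 20% | 0.5 | 33% | 34% |
| 2-fold, both arms, throughout | 50% | 2 | 54% | 55% |
| Procedural only: 1.6%/13.8% once in the stenting arm, 7% a year background in both arms | 50% | none beyond the procedure | 21.0% | 21.4% |

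At 8.6-fold, 20% distal and true HR 0.5, the median hazard ratio was 0.54 unadjusted and 0.51 stratified. In the procedural-only case it was 1.50 and 1.52.

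**The case against.** **Silence is not a decision.** A journal article commonly leaves the covariates of a secondary model, and tables by subgroup, to the full protocol or analysis plan, and neither is shown. This stands for the Cox model. A reader might infer that the plan has chosen an unadjusted model; the text names no stratum but excludes none.

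**The 8.6-fold ratio is not a forecast.** Background says that the distal series included basilar lesions and many more acute-phase procedures, and the plan doubts that the rate applies after that phase. The Discussion describes the review's groups as extracranial and intracranial, whereas the trial divides origin from everything beyond it, which takes in extracranial segments too. So 13.8% cannot simply be assigned to the trial's distal stratum. This stands, but it does not argue for pooling: if the distal rate is unknown, it is a quantity worth estimating separately.

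**The 7.8% is illustrative.** A reader might infer that it is a blend of 1.6% and 13.8%, valid only with about 51% distal lesions. The plan instead sets it beside the 8.2% reported for carotid stenting, to show precision. That inference fails.

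**The procedural ratio should not drive the Cox model.** Medically treated patients have no procedure. Spreading an 8.6-fold hazard over both arms for years is an assumption, and without it the loss nearly disappears. This stands.

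**The DMSC already sees unblinded data.** It receives every outcome event and location is recorded, so it could look by location. That is true, but the criterion offered to it concerns one overall rate.

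**Conclusion.** The point holds, chiefly for the 30-day complication rate. It is the main safety result, it is described only in pooled form, and it depends on a mix the article does not state. On the cited stroke-or-death figures the pooled rate would move from 2.8% to 7.7% as the distal share goes from 10% to 50%. The real contrast in post-acute patients is unknown and may be smaller. The conclusion needs only that risk differs by location to some useful degree, which the investigators' own choice of allocation factor implies.

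The Cox part is minor. Stratifying gains about 8 points of power at HR 2 with half the lesions distal, if location multiplies hazard 8.6-fold in both arms throughout. The gain is about one point at 2-fold and less if the effect is procedural only. A reader might infer that the planned comparison is invalid. It is not: leaving location out is conservative, and the comparison is an additional one in a feasibility study.

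**What to change.** 1. Report the 30-day complication rate with exact 95% interval for origin and for more distal stenoses, beside the pooled rate, and give the origin/distal mix.
2. Show the DMSC the complication rate in the same form. This concerns what is displayed; no change to the stopping criterion is proposed here.
3. State that the Cox model is stratified by location, or confirm that the full analysis plan already says so.

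The cost is a few lines of wording, since location is already recorded for allocation and at baseline. The drawback is imprecision: with 45 patients in each group, 1/45 has an interval of 0.1 to 11.8% and 6/45 one of 5.1 to 26.8%. These overlap, so the rates by location should be presented as descriptive and not as a test of difference.

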## Study design

This is a randomised, open, multi-centre clinical trial with masked outcome assessment, comparing the combination of vertebral artery stenting and best medical treatment with best medical treatment alone in patients with a recently symptomatic stenosis of a vertebral artery of at least 50%. A total of 180 patients will be included. Follow-up will continue until one year after inclusion of the last patient.

Endovascular treatment will be performed by an experienced interventional radiologist with a track record of at least 50 interventions in the carotid or vertebral arteries in the last 5 years. The procedure will include percutaneous transluminal angioplasty followed by stenting. The type of stent and the use of a protection device will be left to the discretion of the interventionist. If stent placement is not feasible or deemed contra-indicated, angioplasty without stent placement will be performed. The procedure will be performed under local anaesthesia, with continuous monitoring of heart rhythm and blood pressure. All patients randomised to stenting will receive clopidogrel 75 mg daily starting at least five days before the procedure and continued for 30 days after the procedure. Patients not on clopidogrel the day before the procedure should be loaded with 300 mg clopidogrel at least six hours before stenting. Best medical treatment will be left to the discretion of the neurologist, but should include rigorous control of vascular risk factors, the use of antiplatelet agents, and the use of a statin.

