### Outcome assessment

Clinical outcome assessment will be performed by three independent adjudicators on the basis of an anonymised written description of the outcome event and ancillary investigations. This description will be made by the research physician in such a way that the adjudicators will remain masked to the allocated treatment.

The primary outcome measure will be vascular death, non-fatal myocardial infarction, or non-fatal stroke (neurological deficit lasting longer than 24 hours for which no other cause than a stroke can be found) within 30 days after start of the treatment (see Appendix for definitions).

Secondary outcome measures will be vascular death, non-fatal myocardial infarction, or non-fatal stroke during follow-up. Other outcome measures include any stroke in the supply territory of the symptomatic vertebral artery during follow-up and the degree of stenosis of the symptomatic vertebral artery after one year, as assessed with both Duplex ultrasound and CT angiography.

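### The between-arm comparison is a single Cox hazard ratio, although the plan's own figures imply strongly non-proportional hazards, so its size depends on length of follow-up

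*Protocol article*

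**What the plan says.** All of this is in the protocol article.

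- **The comparison.** Statistical considerations: "An additional analysis will be done to compare the incidence of vascular events between the two treatment groups". It follows intention to treat and is given as a "hazard ratio with corresponding 95% confidence intervals calculated with the Cox proportional hazard model". No split in time and no risk difference at a fixed time is named.
- **Stenting arm.** Same section: "With 90 patients in the endovascular intervention arm, a complication rate of 7.8% (7 events) would yield a 95% confidence interval from 3.2 to 15.4" per cent. No time window is attached there, but the section adds "The estimate of 7.8% is comparable to that of 8.2% for carotid stenting". Background gives that 8.2% as a 30-day incidence, and Outcome assessment defines the primary outcome as events "within 30 days after start of the treatment".
- **Medical arm.** Same section: 225 patient-years, with a 95% interval of "4.1 to 11.5% for an annual event rate of 7" per cent.
- **Follow-up.** Study design: "Follow-up will continue until one year after inclusion of the last patient". With three years of inclusion, a patient is followed for about 1 to 4 years, depending on entry date.
- **Late effect of stenting.** No event rate after day 30 is given for the stenting arm. Ethical considerations say that endarterectomy lowers long-term stroke risk despite its procedural risk, and that it is not known whether the same is true of vertebral stenting.

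**The concern.** A Cox model with one treatment term assumes that the hazard ratio is the same throughout follow-up. Stenting concentrates its risk around the procedure, while the medical arm is described by an annual rate. If the true ratio is high in the first month and much lower later, the fitted ratio is an average of the two. Its weights depend on how many events fall early and late, and so on how long patients are followed.

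Follow-up here is tied to inclusion of the last patient, so recruitment speed enters the estimate. According to Study objectives, the results are meant to help design a larger trial. A ratio that reflects this trial's mix of follow-up times would not carry over to a trial with a different mix, even if the treatment effects were identical.

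**Working it through.** **1. The plan's own figures reproduce.**
- 7/90 = 7.8%; the exact (Clopper-Pearson) 95% interval is 3.2 to 15.4%.
- 90 × (3/2 + 1) = 225 patient-years.
- 7% × 225 = 15.75, rounded to 16 events; the exact Poisson interval over 225 patient-years is 4.1 to 11.5% per year.

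**2. Hazard ratio in the first 30 days.**
- Stenting: −ln(1 − 7/90) / (30/365.25) = 0.0810 / 0.0821 = 0.986 per year.
- Medical: 0.07 per year, a 30-day risk of 1 − exp(−0.07 × 0.0821) = 0.57%.
- Ratio: 0.986 / 0.07 = 14.1.

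Proportional hazards would require the stenting arm to stay near 0.99 per year after day 30.

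| Change of input | Early ratio |
|---|---|
| Stenting risk 6.4% (Background) | 11.5 |
| Stenting risk 1.6%, proximal (Background) | 2.8 |
| Stenting risk 13.8%, distal (Background) | 25.8 |
| Medical rate 11.5% or 4.1% per year (planned interval limits) | 8.6 or 24.0 |
| Medical 30-day risk 2% or 4% (assumed) | 4.0 or 2.0 |

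**3. What one Cox ratio would estimate.** The medical hazard is 0.07 per year throughout. The stenting hazard is 0.986 to day 30 and r × 0.07 afterwards. The ratio r is an assumption, because the article gives none. The large-sample Cox ratio θ solves

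∫ G(t) [S₁h₁(1 − w) − S₀h₀w] dt = 0, with w = θS₁ / (θS₁ + S₀),

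where G is the proportion not yet censored, and S and h are event-free survival and hazard by arm (1 = stenting, 0 = medical).

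| r | 1 year | 2 years | 4 years | Uniform 1 to 4 years (as planned) |
|---|---|---|---|---|
| 0 | 1.20 | 0.61 | 0.31 | 0.49 |
| 0.25 | 1.43 | 0.85 | 0.56 | 0.74 |
| 0.5 | 1.66 | 1.10 | 0.81 | 0.99 |
| 0.75 | 1.89 | 1.34 | 1.06 | 1.23 |
| 1 | 2.12 | 1.58 | 1.31 | 1.48 |

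Hand check for r = 1, using the ratio of cumulative hazards:
- 1 year: (0.0810 + 0.07 × 0.918) / 0.07 = 2.07.
- 4 years: (0.0810 + 0.07 × 3.918) / 0.28 = 1.27.

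Both are close to the Cox values.

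**4. When the direction changes.** Every row is above 1 at 1 year. At 4 years the ratio equals 1 at r = 0.69, so it changes sides between 1 and 4 years only below that value. Under the planned follow-up it equals 1 at r = 0.51.

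**5. Effect of an early medical-arm peak (assumed).** With r = 0.5 the ratio runs from 1.37 at 1 year to 0.77 at 4 years if the medical 30-day risk is 2%, and from 1.10 to 0.71 if it is 4%. With r = 1 it runs from 1.75 to 1.24 and from 1.40 to 1.15.

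**6. Precision.** Take 4% per year after day 30 as an assumption (r = 4/7 = 0.57). The planned follow-up then gives about 14.6 + 14.3 = 29 first events and a ratio of 1.06. The standard error of its logarithm is about √(1/14.6 + 1/14.3) = 0.372, so the 95% interval is about 0.51 to 2.2. Expected events run from about 21 at r = 0 to 34 at r = 1.

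**The case against.** - **Direction.** A reader might infer that crossing hazards are built into the plan, so that the same truth must read as harm or benefit depending on recruitment. The article does not support this. It needs a late benefit large enough to bring r below about 0.69. The article gives no such rate, and says in Background that stenting has no proven benefit. At r = 0.75 or 1 the ratio stays above 1 at every horizon. This objection stands.
- **The 14-fold figure.** Both planning values illustrate precision, and the ratio assumes a flat medical hazard. Discussion reports that early recurrence is probably raised after vertebrobasilar events, although enrolment up to 180 days after symptoms makes it uncertain how far that applies. This stands as a reason to give a range. At an early ratio of 2 to 4 the hazards are still not proportional unless r is similar.
- **Consequence.** The comparison is labelled additional, the 30-day risk is the primary outcome, and the medical-arm rate is estimated separately. Only those two estimates have a stated precision. A reader might infer that the Cox ratio is meaningless or useless for the later trial. That goes too far: it is an average, but one tied to this trial's follow-up.
- **Noise.** With about 29 events, movements such as 1.10 to 0.81 lie well inside the interval. This is true. It limits what any summary can show, but does not favour one that mixes two periods.
- **Remedy.** A 1-year risk difference alone is also tied to a horizon and discards later scheduled follow-up. This stands, so 1 year should not be the only time point.
- **Detail left elsewhere.** Checks of proportionality may well sit in a fuller plan, and their absence here is not the point. The article itself chooses the single ratio as its measure.

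**Conclusion.** The point holds in a limited form. The planning values imply strongly non-proportional hazards: an early ratio of about 14, or about 2 to 4 under a 4% or 2% medical 30-day risk or the cited 1.6% proximal risk. The size of the single Cox ratio therefore depends on follow-up in every scenario examined, including no late benefit (2.12 at 1 year, 1.31 at 4 years, 1.48 as planned). A change of direction is possible but is not implied by the article.

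The conclusion rests on three assumptions: the 7.8% is a 30-day risk, hazards are constant within each period, and entry is uniform over three years. The value 0.69 also depends on the 7.8% and 7% planning values. Because the comparison is additional and the 30-day risk is reported separately, this is a moderate weakness in a secondary summary and does not undermine the trial's main estimates.

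**What to change.** Keep the comparison by intention to treat and replace the single ratio with:

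1. separate hazard ratios for 0-30 days and after 30 days;
2. Kaplan-Meier cumulative incidence by arm, and risk differences with 95% confidence intervals, at 30 days, 1 year and a later time such as 2 years;
3. the overall Cox ratio, labelled as a descriptive average over the follow-up achieved.

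State one time origin for both arms. The Follow-up section counts visits from stenting in one arm and from randomisation in the other, and the enrolment criteria allow up to two weeks between the two. If randomisation is chosen, a procedure on day 14 has only 30 − 14 = 16 days before the 30-day cut. The complication rate counted from start of treatment should therefore still be shown beside it.

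The cost is analysis wording only: no extra patients, visits or data. The downside is imprecision. In the 4% per year scenario the 1-year risks are 11.1% and 6.8%, a difference of 4.3 points with a half-width of 1.96 × √(0.111 × 0.889/90 + 0.068 × 0.932/90) = 8.3 points. The 2-year difference will be less precise still, because patients who entered late will not have been followed that long.
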